**Design:**

This is a single-center, double-arm, open-label, randomized interventional feasibility study. Our cardio-oncology cohort of > 4000 individuals from our Clinical Research Data Warehouse will be queried to identify at least 200 adult cancer survivors who meet the eligibility criteria. Study participants will be randomized into either the Clinical Decision Aid Group (where patients will use the clinical decision aid in addition to current practice) or the Control Group (current practice). The primary endpoint of this study is to assess for each patient encounter whether cardiovascular medications and imaging pursued were consistent with current medical society recommendations. Additionally, the perceptions of using the clinical decision tool will be evaluated based on patient and physician feedback through surveys and focus groups.

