### Follow-up clinic visits

Follow-up clinic visits may be pursued as clinically indicated. Patients in the Clinical Decision Aid Group may again use the clinical decision aid, which would be an updated version incorporating some of the focus group feedback and suggestions. In addition, study participants in the Control Group will receive their risk group information at the end of the study if desired and can review again at that time with their clinicians the preventive steps they have taken for heart health.

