### Primary endpoints

Chart reviews will also be completed for all patients to assess medication use and imaging patterns in accordance with cardio-oncology recommendations at three and six months after the baseline clinic visit, as the primary endpoints.

If the patient chooses not to or is unable to pursue the recommendations suggested by the clinical decision aid as discussed by the physician, this would be noted in the chart. Therefore, if the physician offers the recommendation, this will be considered consistent with the society statements, even if the patient chooses not to follow the recommendation. An adjudication committee of 3 people may be established to decide what is considered consistent with evidence-based recommendations. If 2 of 3 people agree, that would be considered consistent with evidence-based recommendations.

Success will be determined by ≥ 85% of clinic visits using the clinical decision aid resulting in pursuit of medication use and cardiac imaging surveillance patterns commensurate with recommendations specific to cancer survivors, with overall rates the same or higher than the group without the clinical decision aid, as well as overall favorable patient and physician focus group comments and survey responses.

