### Statistical methods

#### Sample size and power analysis

Assuming 40% consistency with evidence-based recommendations at baseline for both groups [18, 20, 40], we will consider clinical significance at a 50% increase from baseline, which corresponds to 60% consistency with the recommendations. To go from 40% at baseline to 60% in the intervention arm of the trial (i.e., Clinical Decision Aid group) with 80% power requires 97 patients in each group, or 194 total patients. We may be powered to detect such a clinically reasonable change in the primary endpoint. Although we may be powered for this modest change, we could also consider a greater increase from baseline. To go from 40 to 85% with 80% power requires 17 patients in each group, or 34 total patients. We would also be powered for this, but this increase may not be reasonably obtainable.

In this feasibility study, the total number of patients will be limited to 200. One cohort of 100 patients will have clinic visits with current practice plus the clinical decision aid. The other cohort of 100 patients will have clinic visits with current practice alone. This should allow for capturing a variety of cancers and include ethnic minorities in each group.

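### The 85% success rule counts clinic visits in which the aid was used, while randomisation and sample size count patients, so non-use can drop out of the success rate

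*Protocol article*

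**What the plan says.** The protocol article describes the primary outcome in three ways.

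- Abstract, Design: the endpoint is to assess "for each patient encounter whether cardiovascular medications and imaging pursued were consistent with current medical society recommendations". The unit is the encounter.
- Primary endpoints, first paragraph: "Chart reviews will also be completed for all patients to assess medication use and imaging patterns", at three and six months. The unit is the patient at a fixed time.
- Primary endpoints, success rule: at least 85% "of clinic visits using the clinical decision aid resulting in pursuit of medication use" and imaging in line with recommendations for survivors, "with overall rates the same or higher than the group without the clinical decision aid". Favourable survey and focus-group feedback is also required. The unit is the visit, qualified by use of the aid.

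Under Recruitment & randomization, individual patients are allocated, 100 per arm. Under Sample size and power analysis, going from 40% to 60% "with 80% power requires 97 patients in each group, or 194 total patients".

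Neither the number of visits nor use of the aid at each visit is fixed. Under Follow-up clinic visits: "Follow-up clinic visits may be pursued as clinically indicated", and "Patients in the Clinical Decision Aid Group may again use the clinical decision aid". Under Clinical visits and clinical decision aid intervention, the physician reaches the aid through a link in the chart.

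**The concern.** The success rule decides whether the trial is reported as having worked. If it is applied as worded, an aid-arm visit in which nobody opened the tool is not scored as a failure; it disappears from the calculation. The stated objectives are feasibility, acceptability and utility, so those visits are informative, and the rule cannot see them. The qualifying visits are also selected by what physicians and patients do after randomisation, and may be the ones where concordance was easier to reach.

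The visit unit raises a second, separate matter. A patient with three qualifying visits enters three times and a patient with one enters once. The percentage then describes visits made by frequent attenders more than it describes the 100 patients randomised to the aid.

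**Working it through.** **1. The plan's own sample size.** Inputs from the sample size section: 40% versus 60%, 80% power. The significance level of 0.05 is from the data analysis section; two-sided is assumed, since the article does not say. With the pooled-variance formula, equal groups and no continuity correction:

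n = [1.96·√(2·p̄·q̄) + 0.842·√(p₁q₁ + p₂q₂)]² / (p₂ − p₁)²

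- 40% vs 60%: p̄ = 0.50; [1.96·√0.50 + 0.842·√0.48]² / 0.04 = 96.9, so 97 per group.
- 40% vs 85%: p̄ = 0.625; [1.96·√0.46875 + 0.842·√0.3675]² / 0.2025 = 16.9, so 17 per group.

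Both stated figures are reproduced, and power with 100 per arm is 81%. The sample size is not wrong. The formula assumes one independent yes/no outcome per patient, which is not the unit of the abstract's endpoint or of the success rule.

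**2. Effect of leaving out non-use.** The article gives no usage rate and no concordance rate for visits without the aid, so both are assumptions. Let u be the share of aid-arm visits in which the aid is used, 85% the concordance in those visits (exactly at the threshold), and 40% the concordance in the rest (the baseline figure in the sample size section).

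Rate over all aid-arm visits = u × 0.85 + (1 − u) × 0.40

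| Use u | Calculation | All aid-arm visits | Rate under the rule as worded |
|---|---|---|---|
| 100% | 0.850 + 0 | 85.0% | 85% |
| 90% | 0.765 + 0.040 | 80.5% | 85% |
| 80% | 0.680 + 0.080 | 76.0% | 85% |
| 70% | 0.595 + 0.120 | 71.5% | 85% |

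The 85% element is met in every row, although the arm as a whole is below 85% in every row with any non-use.

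**3. The same relation in reverse.** For all aid-arm visits to reach 85%, concordance when the aid is used must be (0.85 − 0.40 × (1 − u)) / u. That is 0.81/0.90 = 90.0% at 90% use and 0.77/0.80 = 96.3% at 80% use. At 70% use it is 0.73/0.70, which exceeds 100%: even perfect concordance when the aid is used gives only 0.70 + 0.12 = 82%.

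**4. Repeat visits.** The article gives no visit counts, so the extra weight on frequent attenders cannot be sized. Its direction depends on whether they are more or less concordant than others.

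**The case against.** The strongest reply is that the phrase is loose wording for the arm. Secondary endpoints and Data analysis both describe the randomised groups by whether they use the aid, and Data analysis equates patients who use it with the Clinical Decision Aid Group. The study design section says clinicians will use the aid with patients, and the chart link can be read as an access route rather than an option. This reading is plausible. If it is the intended one, the exclusion of non-use is removed by a change of wording. It does not resolve the unit: the rule would still count visits, with their number set by clinical indication, against a design that counts patients.

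A reader might go further and infer that repeat visits are analysed as independent, with inflated type I error. The article does not support that. It nowhere says that visits are pooled as independent rows. It names chi-square, Fisher's exact and logistic methods for survey scores, and attaches no test or interval to the 85% threshold.

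A reader might also infer that the randomised comparison is broken. That is not shown either. Charts of all patients are reviewed at three and six months, and Data analysis takes randomised group as the independent variable and compares the groups at single time points.

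Finally, analysis sets and methods for clustering are commonly left to a fuller document, so their absence is no fault. The fault is that the units the article does state disagree.

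**Conclusion.** The concern holds for the success criterion and for the unit of the primary endpoint, and no further. The article fixes a success rate per visit, and an endpoint per encounter, for a trial randomised and sized per patient. Taken literally, the criterion is also conditional on use of the aid after randomisation. On the assumed 85% and 40% concordance rates, the criterion can be met while the rate over all aid-arm visits is 4.5, 9.0 or 13.5 percentage points below the threshold, at 90%, 80% or 70% use. The size depends wholly on those assumptions. That the verdict can differ between the two denominators needs only that use is incomplete and concordance is lower without the aid. The sample size and the comparison by randomised group stand.

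**What to change.** Define the success rate as the proportion of all patients randomised to the Clinical Decision Aid Group who are concordant at one named chart-review time (three or six months), whether or not the aid was opened. Compare it with the same proportion among all patients randomised to control. Report the proportion of aid-group patients whose aid was opened as a separate feasibility result. Bring the abstract, the Primary endpoints section and the sample size section to this one unit. Any rate per visit, or per visit with the aid, can be given as supportive, with allowance for clustering within patient.

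The cost is mainly wording. Chart review of all patients at both times is already planned, and 97 per group still applies because the 60% is stated for the intervention arm. A record of whether the aid was opened is needed. The downside for the sponsor is that the aid-group rate may look less favourable, since patients whose aid was never opened now count. The choice of time and denominator should be made before outcome data are reviewed.

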### Secondary endpoints

Survey responses will be reviewed to determine the impact of the use of the clinical decision aid, in addition to current practice, on cancer survivors’ perceptions of the tool and heart health-related behaviors. The percentages of favorable survey responses and scoring tool results in the patient group using the clinical decision aid will be compared to results from the patient group that does not use the clinical decision aid. A high score will indicate favorable responses for a particular survey, demonstrating favorable perception of the tool regarding the survey topic. We anticipate ≥ 80% of survey questions scored favorably by the group of patients who use the clinical decision aid, with scores the same or higher than the group without the clinical decision aid [39].

Clinically indicated lab values such as troponin, NT-pro-BNP, potassium, and lipid panel, along with BMI, will also be reviewed.

### Exploratory endpoints

Overall favorability of the clinical decision aid will be evaluated using patient and physician focus group comments collated qualitatively. Cancer survivors and physicians will be asked to comment on particular features of the clinical decision aid that contribute to improving usability, understandability, and visual acceptability of the clinical decision aid. This will help us identify ways in which the clinical decision aid tool can be further improved for use by both patients and clinicians.

### Statistical methods

#### Sample size and power analysis

Assuming 40% consistency with evidence-based recommendations at baseline for both groups [18, 20, 40], we will consider clinical significance at a 50% increase from baseline, which corresponds to 60% consistency with the recommendations. To go from 40% at baseline to 60% in the intervention arm of the trial (i.e., Clinical Decision Aid group) with 80% power requires 97 patients in each group, or 194 total patients. We may be powered to detect such a clinically reasonable change in the primary endpoint. Although we may be powered for this modest change, we could also consider a greater increase from baseline. To go from 40 to 85% with 80% power requires 17 patients in each group, or 34 total patients. We would also be powered for this, but this increase may not be reasonably obtainable.

In this feasibility study, the total number of patients will be limited to 200. One cohort of 100 patients will have clinic visits with current practice plus the clinical decision aid. The other cohort of 100 patients will have clinic visits with current practice alone. This should allow for capturing a variety of cancers and include ethnic minorities in each group.

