***Pre-Existing Cardiovascular-Related Medications***
*Patient already on ACE Inhibitor*
*Patient already on ARB*
*Patient already on Beta Blocker*
*Patient already on Statin*
*Patient already on Other Cardiovascular Medications*
*Patient already on Antidiabetic Medication*

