### Study population

The overall study cohort dataset of > 4,000 individuals includes demographic, physiological, laboratory, medication, medical history, and outcomes data relevant to cardiovascular risk stratification in individuals with a history of cancer, as well as cardiovascular imaging reports [30]. This cohort will be queried to identify ≥ 200 adult cancer survivors (including ethnic/racial minorities) clinically considered to be at intermediate, high, or very high cardiovascular risk following cancer therapy determined imprecisely based on demographic and comorbidity information [3, 11, 31–34].

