### Recruitment & randomization

From among these same ≥ 200 patients, our team will partner with the patients’ primary care providers (PCPs), hematologists, or oncologists to recruit and consent 200 adult cancer survivors for clinic visits and focus groups for the remainder of the study. The study team members will contact each potential patient to gauge their interest to participate in the study. Potential study participants who exhibit interest and/or agree to enroll in the study will be provided an information packet containing an informed consent form that offers a more in-depth description of the study and contact information if they are to have additional questions. Those who do not express interest in the study will be noted and no longer contacted. Study participants will be randomly distributed into either the Clinical Decision Aid Group (where *N* = 100 patients will use the clinical decision aid in addition to current practice) or the Control Group (where *N* = 100 patients will only have access to current practice) based on the following stratification factors: sex and race/ethnicity. In collaboration with our biostatistician, patients will be randomly distributed into one of these two arms based on the following stratification factors: sex (2: male, female) and race/ethnicity (3: White, Black, other).

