Simple group comparisons will be made using the chi-square or Fisher’s exact test as appropriate for binary survey score variables. Logistic regression will also be used to estimate the effect of the randomized group on the binary score for each survey question, to allow us to adjust data for the following baseline socioeconomic demographics: age, sex, and level of education if known. These demographic characteristics will also be investigated as potential predictors using multivariate analyses, for survey questions or short-term outcomes with results significantly different between the two randomized groups. Continuous variables will be expressed as mean with standard deviation, whereas dichotomous variables will be expressed as percentages. For continuous characteristics or outcomes, Wilcoxon rank sum test or two-sample t-test will be used as appropriate. Statistical data will be expressed as odds ratio with confidence interval or mean with standard error. Statistical significance will be accepted as *P*-value of < 0.05.

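### Pre-visit concordance with recommendations is assumed at 40% and its ingredients are collected, but it is not named as a stratifier, covariate or subgroup, so the arm comparison forgoes precision and mixes carried-over with new concordance

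*Protocol article*

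**What the plan says.** The population is described under Study population as adult cancer survivors "clinically considered to be at intermediate, high, or very high cardiovascular risk following cancer therapy determined imprecisely based on demographic and comorbidity information". The text shown has no condition that current care must fall short of recommendations.

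Under Sample size and power analysis the plan begins from "Assuming 40% consistency with evidence-based recommendations at baseline for both groups". The target is worded "To go from 40% at baseline to 60% in the intervention arm of the trial", and this "with 80% power requires 97 patients in each group, or 194 total patients". Enrolment is capped at 200, 100 per arm.

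Under Primary endpoints, chart review at three and six months scores whether medication use and imaging accord with recommendations. A physician's offer counts as consistent even if the patient declines. The success criterion is a proportion of all visits that used the aid.

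Table 2 separates drugs already taken (for example "Patient already on Statin") from drugs prescribed, and imaging recently obtained from imaging ordered. All four blocks stand under primary outcomes.

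The design and analysis choices that the article names are:
- Randomisation is "based on the following stratification factors: sex (2: male, female) and race/ethnicity (3: White, Black, other").
- Possible subgroups (Data analysis) are patient-similarity risk cluster, race and sex.
- Adjustment covariates (Data analysis) are age, sex and education, introduced for the survey-question regressions.

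Pre-visit concordance appears in none of these.

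**The concern.** The aim is to learn whether the aid changes care. If a sizeable share of patients arrive with care that already follows recommendations, and most of them remain so, they count as successes in either arm for reasons that have little to do with the aid. The raw rate in each arm is then a blend of carried-over and newly achieved concordance.

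Two things are at stake. The first is precision. Pre-visit status is likely to be a strong predictor of the endpoint, and with enrolment capped at 200 a good baseline predictor is one of the few ways left to sharpen the comparison. The second is interpretation. The same pair of raw rates can correspond to quite different rates of change among the patients who had a gap in care.

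Listing the pre-existing items as primary outcomes adds to the problem. They describe the state before the aid was used and cannot respond to it.

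**Working it through.** **Inputs from the protocol article.** Baseline rate 40% in both groups; target 60%; 80% power; 97 per group; 100 per arm planned (all Sample size and power analysis). Significance level 0.05 (Data analysis): "Statistical significance will be accepted as *P*-value of < 0.05". Sidedness is not stated.

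**Assumed.** Of the patients in each arm, 40% are concordant before the visit. A fraction s of them stay concordant, the same in both arms. The document gives no value for s, so a range is shown.

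**1. The plan's own figures.** The normal-approximation formula for two proportions, with pooled variance under the null, two-sided 5% and no continuity correction, gives 97 per group for 40% versus 60% and 17 per group for 40% versus 85%. Both match the article. Power with 100 per arm is 81% by formula and about 82–83% by simulation of the pooled z-test. The arithmetic is not at fault.

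**2. What the raw rates imply.** The overall rate is 0.4s + 0.6c, where c is the share of initially non-concordant patients who become concordant. Fixing the overall rates at 40% (control) and 60% (aid) gives c₀ = (0.40 − 0.4s)/0.6 and c₁ = (0.60 − 0.4s)/0.6.

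| s | c₀ (control) | c₁ (aid) |
|---|---|---|
| 100% | 0% | 33.3% |
| 90% | 6.7% | 40.0% |
| 80% | 13.3% | 46.7% |
| 70% | 20.0% | 53.3% |
| 60% | 26.7% | 60.0% |

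The difference is always 0.20/0.6 = 33.3 points, but the same 40% versus 60% is compatible with an aid-arm conversion anywhere from one third to 60%. Likewise, with s = 100%, the 85% success level means converting (0.85 − 0.40)/0.6 = 75% of those with a gap. The raw rate shows none of this.

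**3. Power with and without pre-visit status.** Simulated trials, 100 per arm, two-sided 5%; unadjusted pooled z-test against a Mantel-Haenszel test stratified by pre-visit status.

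| s | Unadjusted | Stratified |
|---|---|---|
| 90% | about 82–83% | about 97% |
| 80% | about 82–83% | about 91% |
| 70% | about 82–83% | about 85% |
| 60% | about 82–83% | about 82% |

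**4. How much chance imbalance matters.** The between-arm difference in pre-visit concordance has SD √(2 × 0.4 × 0.6/100) = 6.9 points. It reaches the result only with weight (s − c) in each arm. The SD it contributes is √[(s − c₀)² + (s − c₁)²] × √(0.4 × 0.6/100), where the last factor is 4.9 points.

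- s = 90%: weights 0.83 and 0.50, giving 4.8 points
- s = 80%: weights 0.67 and 0.33, giving 3.7 points
- s = 70%: weights 0.50 and 0.17, giving 2.6 points
- s = 60%: weights 0.33 and 0, giving 1.6 points

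For scale, the unadjusted standard error of the arm difference at 40% versus 60% is √[(0.4 × 0.6 + 0.6 × 0.4)/100] = 6.9 points. This component is already inside that standard error. Stratifying can remove it.

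**The case against.** Several points on the other side are sound.

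*The 40% may not be a count of patients.* It is an assumption taken from cited sources and may be an encounter-level rate under current practice. A reader might infer that exactly 40 of every 100 enrolled patients arrive fully concordant. The text does not say so, and the full eligibility list is not printed. It does expect a substantial baseline rate, which is enough for the point.

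*Concordant patients are not beyond the aid's reach.* A reader might infer that the aid has nothing to change in them. The endpoint includes imaging surveillance at three and six months. Imaging can fall due again and patients can lapse, so keeping care concordant is something the aid may affect. That stronger reading is not supported.

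*Randomisation protects the comparison.* A reader might infer bias, or that the full 6.9-point imbalance enters the result. Neither follows. The unadjusted test is valid, and imbalance carries through only by persistence minus conversion.

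*The gain depends on an unknown rate.* At 90% persistence, control conversion has to be as low as 6.7%, although control patients also see a study cardiologist and an offer alone earns credit. The 97% figure is the favourable end of the range.

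*The distinction is partly handled.* Data analysis compares medication initiation, imaging ordered and changes between visits. These are component measures. The between-visit changes run from the baseline visit, when the aid is already in use. None is concordance before the visit.

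*An analysis plan may settle the primary model.* It may, and the covariates the article names are attached to survey questions. What the article does fix is the randomisation strata and the placing of pre-existing items among the primary outcomes.

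**Conclusion.** The point holds as one of efficiency and interpretation. The stated sample sizes reproduce and the planned comparison is valid, with about 82% power at 40% versus 60%. But a baseline variable that is likely to predict the endpoint, and whose ingredients are collected, has no named role, and those ingredients are classed as outcomes.

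Using it would raise power to about 97%, 91% or 85% if 90%, 80% or 70% of already-concordant patients stay so, and would make essentially no difference at 60%. Chance imbalance in pre-visit status contributes roughly 1.6 to 4.8 points of SD to the arm difference over the same range. These figures assume 40% pre-visit concordance, equal persistence in both arms and overall rates of exactly 40% and 60%. The direction is robust over the range examined, since the stratified test gains or roughly breaks even throughout. The size of the gain is not known in advance.

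**What to change.** 1. Derive a yes/no pre-visit concordance indicator for each patient from the Table 2 items on medications already taken and imaging recently obtained, following the endpoint rules as closely as the chart allows. Score it before randomisation, or by someone blinded to arm.
2. Move those Table 2 items from the primary outcomes to the baseline variables.
3. Stratify or adjust the primary arm comparison by the indicator. Keep all randomised patients in the comparison.
4. Report by arm the share of initially non-concordant patients who become concordant, beside the overall rates.

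The cost is one additional chart scoring per patient, plus one stratum or covariate in the analysis. The indicator will only approximate the endpoint rule: an offer counts as consistent at follow-up, whereas offers made before the study may not be recorded. Some cases may also need the adjudication that the article foresees for the endpoint. Eligibility and sample size do not change.
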